### 5 STUDY DESIGN AND COURSE OF STUDY

#### 5.1 General Study Design and Justification of the Design

This feasibility trial is a two-arm parallel randomized controlled trial (1:1 allocation ratio) that compares an active and control intervention in terms of blinding success. Based on pre-piloting, enrolled participants will be able to complete outcome assessments and interventions in approximately ten minutes. Individual participants will be assigned a specific time slot during the day of the trial execution. An initial intake form will be filled out by study participants via Research Electronic Data Capture (REDCap 12.5.14) the day before the clinical trial is conducted.

The two tested interventions target the back region and pose minimal risks, even for asymptomatic populations. The active intervention will be operationalized as passive soft tissue mobilization of the lumbar paraspinal muscles with the patient laying in a prone position. The control intervention will be operationalized as a series of bilateral light touches that follow the rhythm of deep breathing of the participant applied at the level of the scapular region and more caudally to the level of the lower part of the rib cage (T12). The control intervention is not known to have any beneficial effects and closely resembles a validated MT sham proposed, thus providing reasonable structural equivalence with respect to the active intervention.

The study population will be restricted to a convenience sample of graduate students from the University of Zurich. There is limited preliminary information regarding the sociodemographic characteristics of this study population and how it may relate to the general graduate student population of Switzerland. It is also unclear how the underlying characteristics of this student population may influence our blinding assessment.

To ensure blinding of participants, outcome assessors and data analysts, the study will be conducted in two different rooms at the University of Zurich. In addition, two different REDCap accounts will be created to prevent accidental unblinding of outcome assessors and data analysts within the REDCap system.

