### 10.1 Sample Size Consideration

A precision-based approach has been used to consider sample size (i.e., width of the 95% CI) for the Bang BI estimates rather than statistical power given this is a methodological feasibility randomised trial. We propose to estimate the Bang BI for each group and present a 95% CI for each mean BI point estimate. For a sample size of 26 participants in total (the maximum given our limited class size), the 95% CI will be the observed BI estimate  $\pm 0.315$  points (0.63 points width of the 95% CI) for the primary outcome measure of the group-specific Bang BI, according to Thompson's method (Eq 1) as described by Landsman and colleagues in their study on sample size calculations for blinding assessments. The small class size will inherently limit the precision of our

estimated BI. Ideally, we would want to carry out this trial in a larger study population of approximately 40 participants (20 per group) for a 0.50 points width of the Bang BI 95% CI.

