### Primary Analysis

Blinding indices  $BI_i$  and their respective 95% confidence intervals as defined by Bang et al. will be calculated for each study arm  $i = 1$  for active and  $i = 2$  for sham

$$BI_i = \frac{(2\bar{r}_{i,i} - 1) \cdot (n_{i1} + n_{i2})}{(n_{i1} + n_{i2} + n_{i3})}$$

The Bang index ranges from  $-1$  (opposite guessing related to unblinding) to  $1$  (complete lack of blinding), and can be interpreted as the proportion of participants who guess the intervention correctly over incorrect guesses, including the “don’t know” answer category. In the above formula,  $\bar{r}_{i,i}$  denotes the proportion of correct guesses across the whole population. Successful blinding in the Blinding Index by Bang et al. was predefined as a value from  $-0.2$  to  $0.2$  in the blinding index point estimate. This range will also eventually be used in our analysis as evidence of successful blinding.

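### At 13 per arm, a Bang index point estimate within ±0.2 cannot serve as evidence of successful blinding, because the protocol's own 95% CI half-width (±0.315) is wider than that margin

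*Protocol*

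**What the plan says.** The primary outcome is participant blinding measured by the Bang index. Section 10.2 (Primary Analysis) computes the index and its 95% CI for each arm separately, then sets a success range of −0.2 to 0.2 for the point estimate, citing a published review. It concludes: "This range will also eventually be used in our analysis as evidence of successful blinding". The interval does not enter that criterion.

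Section 10.1 bases the sample size on precision, not power: "We propose to estimate the Bang BI for each group and present a 95% CI for each mean BI point estimate". The size is fixed by the class: "For a sample size of 26 participants in total (the maximum given our limited class size"). Section 5.1 describes a "two-arm parallel randomized controlled trial (1:1 allocation ratio"), which gives 13 per arm. The stated precision is ±0.315 ("0.63 points width of the 95% CI) for the primary outcome measure of the group-specific Bang BI"), obtained "according to Thompson's method (Eq 1"). Section 10.1 adds that the class size limits precision and that the ideal would be "approximately 40 participants (20 per group) for a 0.50 points width of the Bang BI 95% CI".

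**The concern.** The two sections do not fit together. Section 10.1 offers an estimate with an honest interval. Section 10.2 then attaches a success label to the point estimate alone, using a margin narrower than the interval the design can deliver. An estimate inside ±0.2 is compatible with true values well outside it, and an estimate outside ±0.2 is compatible with perfect blinding.

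This matters because the label belongs to the primary outcome. Sections 2.1 and 2.3 say that the purpose is to learn how well this sham blinds, so that later explanatory trials can use the result. A label that depends largely on sampling error is a poor thing to hand on.

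**Working it through.** **Inputs.** n = 26 in total, 1:1, so 13 per arm (sections 10.1 and 5.1). Half-width 0.315 (10.1). Success range ±0.2 on the point estimate, per arm (10.2). Answers include 'I do not know' (8.2). The protocol states neither a 'don't know' share nor a true index. I assume a share of 0% to 50% and show results for several true values.

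**Step 1: reproduce the stated precision.** Thompson's formula is d = max over m of z(1 − 0.05/(2m)) × √[(1/m)(1 − 1/m)/n]. The maximum is at m = 3, where z²(1/m)(1 − 1/m) = 1.2736.
- n = 13: d = √(1.2736/13) = 0.313, width 0.626 (stated: 0.315 and 0.63).
- n = 20: d = √(1.2736/20) = 0.252, width 0.505 (stated: 0.50).

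Both figures reproduce, with n read as the number per arm.

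**Step 2: set the half-width against the margin.** An observed index of 0, the best case, gives 0 ± 0.315, that is −0.315 to 0.315. This crosses both limits of ±0.2, and any other observed value crosses at least one. So, with the protocol's own precision, no observation places the whole interval inside the range. No assumption about 'don't know' answers is needed here.

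**Step 3: what the rule means in counts.** I read the proportion in the section 10.2 formula as correct guesses among those in the arm who guess. The index is then (correct − incorrect)/13. Since 2/13 = 0.154 passes and 3/13 = 0.231 fails, an arm passes when |correct − incorrect| ≤ 2. For example, 6 correct, 4 incorrect and 3 'don't know' gives 0.154 and passes. Its Wald 95% CI is 0.154 ± 1.96 × √[(10/13 − 0.154²)/13], about −0.32 to 0.62. If one 'don't know' had been a correct guess, the arm would have failed.

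**Step 4: exact pass rates.** With 'don't know' share q and true index B, P(correct) = (1 − q + B)/2 and P(incorrect) = (1 − q − B)/2. The pass rate is the trinomial probability, n = 13, summed over all outcomes with |correct − incorrect| ≤ 2. Hand check at q = 0, B = 0: the difference must be ±1, so 2 × 1716/8192 = 0.419.

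| True index | q = 0% | 10% | 20% | 30% | 40% | 50% |
|---|---|---|---|---|---|---|
| 0 | 0.419 | 0.525 | 0.557 | 0.589 | 0.627 | 0.673 |
| 0.3 | 0.238 | 0.296 | 0.296 | 0.290 | 0.281 | 0.265 |
| 0.4 | 0.147 | 0.180 | 0.169 | 0.152 | 0.130 | 0.100 |
| 0.5 | 0.075 | 0.088 | 0.073 | 0.055 | 0.035 | 0.011 |

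A perfectly blinded arm therefore fails 58% of the time (q = 0%) down to 33% (q = 50%).

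**Step 5: sensitivity to scoring.** Section 10.2 also says the indices use the five-point certainty answers. As an illustration (my assumption), give 'somewhat' half weight, with half of the guesses 'strong' and q from 0 to one third. A perfectly blinded arm then fails about 24% to 34% of the time, and an arm with true index 0.3 passes about 28% to 32%. Letting the 'strong' share run from 25% to 75% widens the failure range to about 16% to 40%.

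**Step 6: what a CI-based reading could deliver.** Thompson's figure is a half-width for single proportions. For the index itself at B = 0, the Wald half-width is 1.96 × √[(1 − q)/13]: 0.54 at q = 0%, 0.49 at 20%, 0.38 at 50%. Bringing it down to 0.2 requires 1 − q ≤ 0.04 × 13/1.96² = 0.135, so about 86% or more 'don't know'; otherwise it needs (1 − q) × 1.96²/0.04 per arm, about 96, 77 and 48 at q = 0%, 20% and 50%. At the other end, with ±0.315 the interval lies wholly above 0.2 only if the estimate exceeds 0.2 + 0.315 = 0.515, meaning at least 7 more correct than incorrect guesses (7/13 = 0.54).

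**The case against.** The best defence is that the protocol hides nothing. The arm-specific CIs are part of the primary analysis, section 10.1 concedes the limited precision, the ±0.2 range is taken from a cited source, and this is a one-day feasibility exercise in a course, described as partly illustrative. Much of that stands. A reader might infer that the plan ignores the CI altogether, and it does not. What is missing is any link between the interval and the success label. Reporting the interval does not alter the stated criterion, and a published convention does not become informative at 13 per arm.

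Two further inferences would go too far. One is that the rule amounts to a coin toss that also passes a quarter of badly blinded arms. A failure rate near one half at true index 0 needs a low 'don't know' share, and a pass rate near one quarter belongs to a true index of 0.3, just outside the margin; by 0.5 it is 1% to 9%. The other is that both arms must pass together, with correspondingly lower chances. The protocol evaluates each arm separately and states no joint criterion.

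It is also fair to say that a CI rule makes the word successful almost unreachable here. That limits what the trial can claim; it is no reason to rest the claim on the point estimate.

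**Conclusion.** The point holds as a defect in the stated interpretation of the primary outcome. It rests first on the protocol's own two numbers: a half-width of 0.315 against a margin of 0.2. That comparison alone shows that a point estimate within ±0.2 is not evidence that the true index is within ±0.2.

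The error rates show the size, and they are conditional on 13 per arm, the three-category formula and an assumed 'don't know' share of 0% to 50%. They are 33% to 58% failure at true index 0, and a pass rate of 24% to 30% at 0.3 and 10% to 18% at 0.4. Certainty weighting lowers the failure rate at 0 in the illustration but leaves the rule a weak discriminator. A reader might also infer that the label would by itself validate or reject the sham. The protocol says only that the results can inform later trials, so the harm is a misleading summary rather than a formal decision.

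**What to change.** In section 10.2, Primary Analysis:
- Delete the statement that the range will count as evidence of successful blinding.
- Make each arm's Bang index with its 95% CI the primary result, and describe ±0.2 as a descriptive benchmark from the cited source.
- If a label is wanted, call blinding successful only when the whole CI lies within ±0.2, unsuccessful only when the whole CI lies outside it, and inconclusive otherwise.
- State in advance that at 13 per arm inconclusive is the expected reading unless the index is far from 0.
- Say whether the five-point answers are collapsed to three categories, as the printed formula implies, or weighted by certainty.

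No participants, visits or data items are added. The cost is that the trial gives up a yes/no claim of successful blinding, which this sample size could not support.

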### Secondary Analyses

For our secondary analyses, we will quantitatively evaluate participant’s blinding with James’s BI. The range of this complementary index ranges from  $0$  (all correct) to  $1$  (all incorrect) and does not provide different values according to intervention. An index of  $0.5$  (half correct, half incorrect) indicates random guessing. In addition, we will also assess blinding index in the outcome assessors using Bang’s BI after completing and documenting measurements at  $T_1$ .

Both blinding indices (Bang and James) will be calculated with the R package {BI} based on the participant responses about their degree of confidence in their assigned intervention group (displayed in 5-point Likert scale format).

In the secondary analysis, the measured change in ROM (maximum flexion and extension) of the thoracolumbar spine will be compared within and between the intervention groups (active vs. control;  $T_0$  vs.  $T_1$ ), although formal statistical testing of difference between groups will not be performed, as this would not align with our primary objective. In case a large difference in baseline characteristics is detected between the groups, regression analysis with adjustment of anticipated confounders (i.e., age, gender, experience with MT, care-seeking history for LBP) may be considered.

Contributing factors to perceived intervention arm allocation in study participants, as well as outcome assessors, will be qualitatively analyzed using thematic analysis. Two study investigators will collate collected responses, group them thematically and develop emerging clusters using a consensus-based approach.

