### Assessment of Secondary Outcomes

#### *Blinding success in study participants*

Blinding success in study participants will be measured with an alternative blinding index – James Blinding Index. Although this index requires different computational considerations, it can be derived from the previously described five-point scale inquiring about the degree of certainty regarding perceived intervention arm allocation (1 = “I strongly believe I received the active intervention”; 2 = “I somewhat believe I received the active intervention”; 3 = “I somewhat believe I received the control intervention”; 4 = “I strongly believe I received the control intervention”; and 5 = “I do not know”).

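### The printed reading key for the James index holds only if nobody answers don't know, although the item behind it offers that answer

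*Protocol*

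**What the plan says.** Section 10.2 (Secondary Analyses) gives three reference points for the James index. Zero stands for everyone guessing correctly. The upper end, 1, is described as "all incorrect) and does not provide different values according to intervention". For the midpoint of 0.5 the wording is "half correct, half incorrect) indicates random guessing". The key mentions no other kind of answer.

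Section 8.2 (Assessment of Secondary Outcomes, participants) says of the James index that "it can be derived from the previously described five-point scale inquiring about the degree of certainty regarding perceived intervention arm allocation". The list of answers there ends with "and 5 = “I do not know". Section 10.2 confirms that these five-point answers are the input: both indices are calculated "based on the participant responses about their degree of confidence in their assigned intervention group".

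The Primary Analysis text treats the Bang index differently. Its interpretation is given as "including the “don’t know” answer category", and a success range of −0.2 to 0.2 is set for it. No success range is set for the James index.

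**The concern.** The item has three kinds of answer (right, wrong, don't know), but the James key interprets only two. In the standard James index a don't-know answer counts towards good blinding and moves the value up towards 1. The values 0.5 and 1 can therefore each arise from quite different sets of answers, and the key names only one for each.

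Blinding success is the primary question of this trial, the James index is a listed secondary outcome (section 4.2), and the results are meant to inform later manual therapy trials (section 2.3). Don't know is also a natural answer from a well-blinded participant. Read by the printed key, a well-blinded group could be reported as guessing wrongly, and a partly unblinded group as guessing at random.

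**Working it through.** **Inputs**
- Reference points 0, 0.5 and 1: protocol section 10.2, Secondary Analyses.
- Five answer categories including don't know: section 8.2.
- 26 participants (section 10.1) allocated 1:1 (section 5.1), taken as 13 per arm.
- Bang success range −0.2 to 0.2: section 10.2, Primary Analysis.
- Proportion answering don't know, P_DK: not in the protocol, so a range is assumed.
- James formula: not printed in the protocol. The standard definition of the named method is used.

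**Formula**

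BI = [1 + P_DK + (1 − P_DK) × K]/2, with K = (P_obs − P_exp)/P_exp.

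P_obs and P_exp are the observed and chance-expected weighted disagreement among those who guess, with weight 0 for correct and 0.5 for incorrect. Let c be the share correct among those who guess. With balanced arms and guesses split evenly overall, P_obs = 0.5(1 − c) and P_exp = 0.25, so K = 1 − 2c and

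BI = 1 − (1 − P_DK) × c.

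**Step 1: the protocol's own key.** With P_DK = 0:
- c = 1 gives 0
- c = 0.5 gives 0.5
- c = 0 gives 1

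All three reference points are reproduced. With arms of 12 and 14, everyone wrong gives 0.994 rather than 1.

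**Step 2: chance guessing with some don't-know answers.** At chance K = 0, so BI = (1 + P_DK)/2 and the shift from 0.5 is P_DK/2.

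| Assumed P_DK | Chance value | Shift from 0.5 |
|---|---|---|
| 1 of 26 | 0.52 | 0.02 |
| 10% | 0.55 | 0.05 |
| 25% | 0.625 | 0.125 |
| one third | 0.67 | 0.17 |
| one half | 0.75 | 0.25 |

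In whole numbers, 4 correct, 4 incorrect and 5 don't know per arm gives 1 − (8/13)(0.5) = 0.692. Two correct, 2 incorrect and 9 don't know gives 1 − (4/13)(0.5) = 0.846. These two values were the same under four sets of weights for strong and weak beliefs, as expected when K = 0.

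**Step 3: cases that the key misdescribes.** Bang is taken per arm as correct minus incorrect, over all answers.

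| Answers | James | Key reads it as | Bang, each arm |
|---|---|---|---|
| All don't know | 1.0 | everyone wrong | 0 |
| Half don't know, all guesses correct | 0.50 | random guessing | +0.5 |
| 7 of 13 per arm correct, 6 don't know | 6/13 = 0.462 | close to random guessing | 7/13 = +0.538 |

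The third row is the nearest whole-number form of the second, since half of 13 is not a whole person. In rows two and three, Bang lies outside −0.2 to 0.2.

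**Step 4: one value, two meanings.** With no don't-know answers and 75% incorrect, BI = 1 − 0.25 = 0.75. With 50% don't know and chance guessing, BI = 1 − 0.5 × 0.5 = 0.75. The index alone cannot separate these, but the don't-know proportion can.

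**The case against.** The strongest reply is that the reference points are true as written. Two halves leave no room for a third answer, and the end points likewise describe everyone guessing. Step 1 bears this out, so a reader who infers that the protocol's figures are arithmetically wrong goes too far. What fails is their use as a general key for an item with a don't-know option: 0.5 is tied to random guessing without that condition, and no other section supplies it.

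A reader might also infer that the James index is the trial's check on its primary result. The protocol calls it complementary and alternative, and nowhere says that it confirms or overrides Bang. Nor does the protocol support saying that the index will be misread. There is no James cut-off, the don't-know share is unknown, and with one such answer among 26 the shift is only about 0.02. Bang is reported per arm with don't know included, and would show the unblinding in rows two and three of Step 3 directly. These points limit the consequence.

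The formula and the weights for strong and weak beliefs are not in the protocol, and the weights may properly be left to an analysis plan. The chance value and the all-don't-know value do not depend on them. The 0.5 with half don't know assumes either strong beliefs or equal weight for strong and weak ones.

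**Conclusion.** The point holds in a limited form. The printed key is right with no don't-know answers and incomplete otherwise, and the item invites such answers. Under the standard James definition the chance value is understated by P_DK/2: 0.05 at an assumed 10%, 0.17 at one third, 0.25 at one half. The value 1 also means complete uncertainty, and 0.5 can accompany clear unblinding. The index could be misread whenever don't-know answers are more than a few. This concerns the interpretation of one secondary outcome without a threshold, and leaves the primary Bang analysis as it is. It is more than missing detail, because the protocol chose to state an interpretation and that interpretation does not fit its own item.

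**What to change.** Restate the key in section 10.2:
- 0: every participant guesses correctly and nobody answers don't know (no blinding).
- 1: everyone answers don't know (complete blinding). With balanced arms, the same value arises when all guesses are wrong.
- Chance guessing: (1 + P_DK)/2, which equals 0.5 only when there are no don't-know answers.

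The lower end should not be shortened to all guesses being correct, because under the formula above that gives P_DK, which is zero only when nobody answers don't know.

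Report the don't-know proportion beside the index and compare the index with the chance value. The cost is two reworded sentences and one extra reported number. Data collection and the primary analysis do not change.

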| Exclusion criterion: pregnancy or breastfeeding                                      | I am currently pregnant or breastfeeding.                                                                          | y/n                  |                 | x              |                |
| Self-reported back function assessment                                               | How would you rate your back flexibility at the moment?                                                            | 5-point Likert scale |                 | x              | x              |
|                                                                                             | Do you currently experience ache, pain, or discomfort in your upper back?                                          | y/n                  |                 | x              | x              |
|                                                                                             | If yes: How uncomfortable do you feel with the ache, pain, or discomfort in your upper back?                       | 3-point scale        |                 | x              | x              |
|                                                                                             | Do you currently experience ache, pain, or discomfort in your lower back?                                          | y/n                  |                 | x              | x              |
|                                                                                             | If yes: How uncomfortable do you feel with the ache, pain, or discomfort in your lower back?                       | 3-point scale        |                 | x              | x              |
| Thoracolumbar spine flexion–extension                                                | Thoracolumbar angle (Smartphone application)                                                                       | Degrees of motion    |                 | x              | x              |
| Blinding success in outcome assessors                                                | To which extent do you know which intervention (active intervention or control intervention) the patient received? | Blinding index       |                 |                | x              |

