#### *Blinding success in outcome assessors*

The Blinding success in the outcome assessors will be measured using the Blinding Index according to Bang. The scale is the same as described for the primary outcome. The question will refer to the degree of confidence of the assessor that participants have received either the active or the control intervention (1 = “I strongly believe they received the active intervention”; 2 = “I somewhat believe they received the active intervention”; 3 = “I somewhat believe they received the control intervention”; 4 = “I strongly believe they received the control intervention”; and 5 = “I do not know”).

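### Assessor guesses recur within the same assessor, yet the arm-specific Bang index counts each one as a separate responder

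*Protocol*

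**What the plan says.** Section 3.2 of the protocol makes blinding of the outcome assessors the first secondary objective. Table 1 in section 7.3 puts the assessor question at T1 and words it for one patient: "To which extent do you know which intervention (active intervention or control intervention) the patient received". Section 8.2 adds "The scale is the same as described for the primary outcome", which carries the participants' five answer options over to assessors. For the analysis, section 10.2 says "we will also assess blinding index in the outcome assessors using Bang’s BI after completing and documenting measurements at $T".

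Under Primary Analysis in the same section, the Bang indices "and their respective 95% confidence intervals as defined by Bang et al. will be calculated for each study arm". Success there is a point estimate between -0.2 and 0.2, and the negative end of the scale is described as opposite guessing linked to unblinding.

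The protocol does not give the number of assessors or the number of patients each one sees. It names no assessor identifier. The only stratification variable is previous experience with manual therapy.

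**The concern.** For participants, each guess comes from a different person, so the Bang index and its multinomial variance suit the data. For assessors, up to 26 guesses come from however many people measure outcomes on one day. An assessor may have no idea of the allocation and still lean towards answering active, or towards answering control, patient after patient. Guesses by the same assessor are then correlated, and each arm's index is more variable than a method for separate responders assumes.

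An arm-by-arm reading can then mistake habit for information. An assessor who mostly answers active scores as correct in the active arm and as wrong in the control arm. Read separately, these results look like failed blinding in one arm and opposite guessing in the other, although nothing leaked. Without an assessor identifier, habit and leaked allocation cannot be separated afterwards.

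**Working it through.** **The plan's own precision figure.** Section 10.1 starts from 26 participants ("For a sample size of 26 participants in total (the maximum given our limited class size") and gives a half-width of 0.315, that is "0.63 points width of the 95% CI) for the primary outcome measure of the group-specific Bang BI". Thompson's formula is n = max over m of z²(1/m)(1 - 1/m)/d², with z the normal quantile at 1 - 0.05/(2m). The maximum is at m = 3, where z = 2.394:
- d = 0.315: 5.731 × 0.2222 / 0.0992 = 12.84, so 13 per arm.
- d = 0.25: 20.4, which agrees with the stated "larger study population of approximately 40 participants (20 per group) for a 0.50 points width of the Bang BI 95% CI".

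Both figures reproduce. They are given for the primary, participant index and take responses as independent. The formula bounds category proportions, so it is not the Bang half-width used below. That difference is a separate matter.

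**Inputs.**
- From the documents: 26 patients, and a "two-arm parallel randomized controlled trial (1:1 allocation ratio", so 13 per arm. Individuals are randomized, so an assessor can see both arms.
- Assumed, because not stated: 1, 2 or 4 assessors seeing patients in rotation; within-assessor correlation (ICC) 0.05 to 0.2; don't-know answers 0%, 30% or 60%.
- Assessors know nothing. Each assessor's tendency to answer active is drawn from a symmetric Beta distribution with mean 0.5, independent of arm.

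**Formulas, per arm.** BI = (correct - incorrect)/13. Independent-response variance = [(correct + incorrect)/13 - BI²]/13. The interval is BI ± 1.96 SE.

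**Analytic check.** With no don't-know answers and BI near 0, SE = √(1/13) = 0.277 and the half-width is 1.96 × 0.277 = 0.544. With 2 assessors there are 6.5 guesses per assessor per arm, and the design effect is 1 + (6.5 - 1) × ICC:
- ICC 0.1: 1.55, so the half-width should be 0.544 × √1.55 = 0.68.
- ICC 0.2: 2.10, so it should be 0.544 × √2.10 = 0.79. The SD of the BI is then 0.277 × √2.10 = 0.40. Simulation gives 0.41, against a mean reported SE of 0.25.

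**Simulation** (40,000 trials per setting, 2 assessors, no don't-know answers):

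| Event when assessors know nothing | Independent | ICC 0.1 | ICC 0.2 |
|---|---|---|---|
| One arm's 95% interval excludes 0 | 9% | 19% | 28% |
| At least one arm's interval excludes 0 | 18% | 33% | 43% |
| One arm's BI outside ±0.2 | 58% | 67% | 72% |
| One arm above +0.2, the other below -0.2 | 17% | 34% | 45% |
| Both arms above +0.2 | 8% | 6% | 5% |
| 95% interval for the sum of the two BIs excludes 0 | 8% | 8% | 8% |

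**Sensitivity to the assumptions.**
- At ICC 0.05 with 2 assessors, the first row is 14%.
- With 4 assessors, it is 14% at ICC 0.1 and 18% at ICC 0.2. With 1 assessor, it is about 28% at ICC 0.1.
- With 2 assessors and 30% don't-know answers, the first row (independent, ICC 0.1, ICC 0.2) becomes 8%, 14%, 21%, and the ±0.2 row 41%, 49%, 56%.
- With 60% don't-know answers, they become 9%, 13%, 17% and 27%, 33%, 37%.

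**The case against.** **No interval or test is set for assessors.** The 95% intervals stand under Primary Analysis. The sentence on assessors names none, and no passage uses an interval that excludes 0 as a verdict. The statement in section 8.2 concerns the response scale, not the variance, and the sentence on the R package refers to participant responses. This stands: carrying the participant interval over to assessors is a natural extension, but it is not written.

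**The only written rule is ±0.2 on the point estimate.** A wider interval would not change that verdict, and most false verdicts come from 13 per arm: 58% even with independent guesses. This also stands. Section 10.1 itself concedes that the class size limits precision.

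**Participants, not assessors, are randomized.** A shared habit therefore raises one arm's index and lowers the other's. A reader might infer that uninformed assessors will too often appear unblinded in both arms. The calculation does not support that: both arms above +0.2 becomes rarer, and the sum of the indices is not inflated. What remains is that the protocol never uses the sum. It defines the index by arm and gives negative values a meaning of their own.

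**Such detail may belong in a separate analysis plan, and assessors also explain each guess.** Section 5.3 names section 10 as the predefined data analysis plan, so the choice of index is fixed there. The open-ended explanations may help to separate habit from information, but nothing links them to the reading of the index.

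**Conclusion.** The point holds in a limited form. Assessor guesses are recorded per patient and summarised by an arm-specific index designed for separate responders. If any assessor sees several patients and has an answering habit, the index in each arm is overdispersed. With 2 assessors and ICC 0.05 to 0.2, an independent-response interval would exclude 0 in about 14% to 28% of no-knowledge trials, against 9%. At ICC 0.1 to 0.2, a single arm falls outside ±0.2 about 9 to 14 percentage points more often than with independent guesses (67% to 72% against 58%). Opposite signs beyond ±0.2 arise in about 34% to 45% of trials against 17%, and an arm-by-arm reading could take that for failed blinding or opposite guessing.

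These sizes rest on an assumed number of assessors and an assumed correlation. They shrink with more assessors, lower correlation or more don't-know answers, and they vanish if each patient has a different assessor. The documents do not support a claim that the trial will report assessors as unblinded. The outcome is secondary, so the change is worth making but does not touch the primary analysis.

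**What to change.** In section 10.2, give the assessor index its own paragraph:
- Store an assessor identifier with each T1 guess, and report the number of assessors and the guesses per assessor.
- Present the assessor Bang index by arm, overall and per assessor, as descriptive, without an independent-response interval and without a ±0.2 verdict for a single arm.
- Read the two arms jointly through the sum of the arm indices, which answering habit does not inflate.
- Optionally, add a reference distribution from permuting allocation within assessor.

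The cost is one extra data field, a few lines of R and a less definite assessor result. The optional permutation is conservative: simulated size was 1.4% to 2.1% at a nominal 5% with 2 or 3 assessors (1,500 trials of 300 permutations each, ICC 0.2 to 0.3). It also does not reproduce the stratified blocked randomization exactly, so it should stay optional in a feasibility trial planned on precision.
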